## 9. ADVERSE EVENTS

All adverse (unfavorable, negative or harmful) events that are related to or possibly related to PP are to be reported by each participating center by the site investigator to the principal investigator on a case specific reporting form and classified as serious if it:

- Results in death
- Is life-threatening
- Requires admission to a higher level of care
- Requires medical or surgical interventions to prevent a more serious adverse event

All serious adverse events will be reported to the trial steering committee within 24 hours of occurrence.

Possible adverse event may be:

- Pressure wounds
- Aspiration
- Cardiac arrest

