## PROTOCOL SYNOPSIS

**English title:** Awake prone positioning with high flow nasal oxygen in critically ill covid-19 patients.

**Swedish title:** Buklägesbehandling med högflödesgrimma vid covid-19.

**Objectives:** Determine if a protocol for prone positioning with high flow nasal cannula or noninvasive ventilation reduces the rate of intubation in awake spontaneous breathing covid-19 patients or patients with other infectious disease with moderate to severe hypoxemic respiratory failure.

**Design:** Multicenter randomized controlled, parallel group, superiority trial.

**Population and Intervention:** 240 adults, 18 years or older with confirmed or strongly suspected infection with novel corona virus SARS-CoV-2 or other infectious disease, ongoing or planned oxygen treatment with high flow nasal cannula or noninvasive ventilation and moderate to severe respiratory failure as defined by a  $\text{PaO}_2/\text{FiO}_2$  ratio of  $\leq 20$  kPa ( $\approx 150$  mmHg) and/or a  $\text{FiO}_2$  of 0.5 required to reach an  $\text{SpO}_2$  of 94%.

Patients will be randomized 1:1 to a prone positioning protocol with a prone position target of 16 hours/day OR standard care.

**Outcomes:** Primary outcome is the rate of intubation. Secondary outcomes include time in prone position, admission to the ICU, time on mechanical ventilation, need for renal replacement therapy, the WHO ordinal scale for clinical improvement and the 7- and 30-day mortality and complication rate.

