## **2.1 Aim(s)**

The primary aim of this study is to determine the effect on prone positioning with HFNC or NIV on the intubation rate in critically ill COVID-19 patients or patients with other infectious disease with moderate to severe hypoxemic respiratory failure. The secondary aims include time/day in PP, 7- and 30-day mortality, days on ventilator, in-hospital and ICU LOS, incidence of RRT, the need for vasopressors and/or inotropic drugs, the WHO ordinal scale for clinical improvement, and adverse events during PP. In a subset of 30 patients we aim to study the acute effects on lung volume and function with EIT, PaO2/FiO2 ratios, respiratory rate, hemodynamic parameters and effect on dyspnea.

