### 7.2 Secondary outcomes

- time in PP/day in awake PP if measured. This will vary at different sites and wards.
- cross-over rate to NIV,
- incidence and days of vasopressor and/or inotropic support,
- incidence and days of renal replacement therapy,
- days on ventilator for patients in need of mechanical support,
- number of patients receiving extracorporeal membrane oxygenation,
- in-hospital and ICU LOS,
- complications.
- the 7- and 30-day mortality.
- WHO ordinal scale (Fig 1) for clinical improvement at baseline, day 7 and 30.

*Fig 1. WHO ordinal scale for clinical improvement*

| Patient State  | Description                                      | Score |
|----------------|--------------------------------------------------|-------|
| Uninfected     | No clinical or virological evidence of infection | 0     |
| Ambulatory     | No limitations of activities                     | 1     |
|                | Limitations of activities                        | 2     |
| Hospitalized   |                                                  |       |
| Mild disease   | No oxygen therapy                                | 3     |
|                | Oxygen by prongs or mask                         | 4     |
| Severe disease | NIV or HFNC                                      | 5     |
|                | Intubation and mechanical ventilation            | 6     |

|      |                                                                              |   |
|------|------------------------------------------------------------------------------|---|
|      | Mechanical ventilation
+additional organ support
(pressors, RRT, ECMO) | 7 |
| Dead | Death                                                                        | 8 |

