## 8.2 Interim analyses

Due to the lack of previous study data and the difficulties in predicting the course of the epidemic in Sweden, we plan to conduct interim analyses after inclusion of 120 and 180 patients. The decision to terminate the study may be based on 1) futility (lack of patients fulfilling the inclusion criteria), 2) safety (unexpected increase in the rate of intubation in the intervention group or increased occurrence of severe or unexpected adverse events, or 3) efficacy (if the reduction in the rate of intubation is more than 40%).

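### Section 9 reports adverse events only when unblinded site staff link them to prone positioning, so harms are ascertained differently in the two arms

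*Protocol*

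**What the plan says.** Protocol section 9 sets the reporting rule: "events that are related to or possibly related to PP are to be reported by each participating center". It then lists the criteria that make such an event serious and adds that "All serious adverse events will be reported to the trial steering committee within 24 hours of occurrence". Under "Possible adverse event may be" it names pressure wounds, aspiration and cardiac arrest. It mentions neither arm and has no instruction to record events whatever their cause.

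Other parts of the protocol use harms as follows:

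- The synopsis lists the "7- and 30-day mortality and complication rate" among the secondary outcomes.
- Section 7.2 (Secondary outcomes) lists "complications", with no definition, time window or source.
- Section 2.1 words the aim as "adverse events during PP".
- Section 8.2 allows the trial to stop for safety on either of two grounds: "unexpected increase in the rate of intubation in the intervention group", or "increased occurrence of severe or unexpected adverse events". No comparator is given for the second.

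Section 6 states that patients, physicians and other carers know the allocation. Blinding of assessors applies to the analysis. The section on the standard care arm (5.1.2) leaves prone positioning to the treating physician's discretion.

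**The concern.** In a randomised comparison of harms, whether an event is counted should not depend on the treatment received. Here it depends on a judgement that the event was linked to the experimental treatment, made by people who know the allocation. None of the three named events is specific to prone positioning. For a control patient who has not been proned, there is nothing to attribute the event to, so the same event is unlikely to be reported.

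Two uses of the data are at stake. A comparison of complications built on these reports would tend to count against prone positioning. A safety review under section 8.2 would see the same imbalance. There is also an opposite risk: a harm caused by the prone protocol but judged unrelated by site staff never reaches the steering committee. Because this is a rule for collecting data, events that were not reported cannot be recovered at analysis.

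**Working it through.** The protocol states no adverse-event rate, safety boundary or safety power, so there is no figure to reproduce. The check has two parts.

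**1. The same event followed through section 9**

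| Patient | Event | Reportable? |
|---|---|---|
| Prone arm, proned | Pressure wound | Yes, a link is at least possible |
| Prone arm, proned | True harm that staff judge unrelated | No |
| Standard care, proned at physician's discretion | Pressure wound | Yes, if staff make the link |
| Standard care, never proned | Pressure wound | Usually not, as there was no exposure to link it to |

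Reporting follows exposure and attribution, not randomised group. Section 8.3 specifies intention-to-treat analyses, which need counts collected alike in all randomised patients. Because the serious criteria classify events already filtered by attribution, the 24-hour report does not close the gap.

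**2. Illustration of possible size (all rates assumed)**

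Inputs from the protocol: 1:1 allocation (section 6), and looks after 120 and 180 patients (section 8.2), hence about 60 and 90 per arm. Assumptions: the true event rate p is the same in both arms, every event in the prone arm is reported, and a fraction c of control events is reported. Reported counts are then Binomial(n, p) and Binomial(n, pc). A harm signal is an uncorrected chi-square with

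z = (a − b)/n ÷ √[2 p̄(1 − p̄)/n] > 1.96, where p̄ = (a + b)/(2n).

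Summing over all pairs (a, b) gives the probability of a spurious harm signal:

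| n per arm | p | c = 0 | c = 0.25 | c = 0.5 | c = 1 |
|---|---|---|---|---|---|
| 60 | 5% | 0.35 | 0.18 | 0.09 | 0.023 |
| 60 | 10% | 0.86 | 0.40 | 0.17 | 0.025 |
| 90 | 5% | 0.66 | 0.28 | 0.12 | 0.021 |
| 90 | 10% | 0.98 | 0.55 | 0.24 | 0.025 |

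At n = 60 and p = 10%, expected reports are 6.0 in the prone arm against 0, 1.5, 3.0 and 6.0 in controls.

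The result also depends on the test. With zero control reports, two-sided Fisher p = 2 × C(n, a)/C(2n, a):

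- Full enrolment, p = 5%: 6/120 v 0/120 gives 2 × C(120, 6)/C(240, 6) = 0.029. With one control report (6 v 1), p = 0.12.
- First look, p = 5%: the expected 3/60 v 0/60 gives 0.24.
- Second look, p = 5%: the expected count is 4.5; 4/90 v 0/90 gives 0.12 and 5/90 v 0/90 gives 0.06.

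**The case against.** The strongest reply has four parts.

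**Control events are not excluded.** Section 9 names no arm, and discretionary proning is allowed in controls, so control events linked to it are reportable. This stands. A reader might infer that control events are not captured at all, or that the control rate is near zero by construction. The protocol does not support that: capture is differential, not shown to be nil.

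**Complications may have another source.** Section 7.2 does not tie the outcome to section 9, and a CRF or SAP that is not at hand could define it for both arms. Section 2.1 can also be read as a purely descriptive aim about events while prone. This stands as a limit: the complication comparison is affected only so far as it rests on section 9 reports. It does not remove the problem, because section 9 as written directs sites to filter by attribution, and the wording in section 2.1 still does not match the synopsis and section 7.2.

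**The safety criterion has another limb.** Intubation does not depend on attribution. Mortality, vasopressor or inotrope use, renal replacement, ventilator days and extracorporeal support do not either. Stopping is discretionary and no threshold is set. All of this stands, so calling the whole safety rule unfair would go too far. None of those outcomes, however, records pressure wounds or aspiration.

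**A false safety stop is not shown.** A reader might take 6/120 v 0/120 as evidence of one. That contrast assumes all-or-nothing capture, an invented 5% rate and full enrolment, while the planned looks come earlier. At those looks the expected counts under the same assumption do not reach p < 0.05 by Fisher's test. This also stands.

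**Conclusion.** The point holds in a limited form. Section 9 ties adverse-event reporting, and with it serious adverse-event reporting, to unblinded attribution to prone positioning, so ascertainment differs by arm. The adverse-event limb of section 8.2 is biased, as is the comparison of complications to the extent that it draws on these reports. The primary outcome, the intubation limb, mortality and the organ-support outcomes are not affected.

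Under-reporting in unproned controls works against prone positioning; harms wrongly judged unrelated work in its favour. The protocol does not settle the net effect, and its size cannot be derived because no event rates are given. The illustration shows only that the distortion need not be trivial and does not require zero capture in controls. Its event rates and capture fractions are assumptions, and its probabilities depend on the test. The change should be made: the rule is explicit, its effect cannot be undone at analysis, and correcting it is cheap.

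**What to change.** 1. In section 9, require the listed events (pressure wounds, aspiration, cardiac arrest) and every event meeting the serious criteria to be recorded in all randomised patients in both arms, over the same time window, regardless of attribution.
2. Record relatedness to prone positioning as a separate field, so that it describes an event and does not decide whether the event is counted.
3. Base the complications outcome in section 7.2 and the adverse-event limb of section 8.2 on these counts by randomised arm, and name the control arm as the comparator.
4. Reconcile the aim in section 2.1, which is limited to events while prone, with the synopsis and section 7.2. If a description of events during prone sessions is also wanted, list it separately from the comparison between arms.

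The cost is a few extra CRF fields, edits to sections 2.1, 7.2, 8.2 and 9, and somewhat more event paperwork in the control arm. Treatment, sample size and the primary analysis do not change.

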### **3.2 Ethical considerations**

Ethical approval will be sought from the Swedish Ethical Review Authority. Written informed consent will be obtained from all participants in the study. This study will be conducted in compliance with all stipulations of this protocol, the conditions of the ethics committee approval, standards of Good Clinical Practice (as defined by the International Conference on Harmonisation), ethical principles that have their origin in the Declaration of Helsinki and all applicable national and local regulations. This study is not sponsored by any commercial entity.

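### The seriousness criteria in section 9 omit lasting disability and prolonged hospital stay, and the interim safety ground in 8.2 uses a different term that is left undefined

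*Protocol*

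**What the plan says.** Section 9 sets the scope of reporting broadly: "All adverse (unfavorable, negative or harmful) events that are related to or possibly related to PP are to be reported" by the site investigator to the principal investigator. Each event is then "on a case specific reporting form and classified as serious if it" satisfies one of four criteria:

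1. "Results in death"
2. "Is life-threatening"
3. "Requires admission to a higher level of care"
4. "Requires medical or surgical interventions to prevent a more serious adverse event"

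Only serious events go to the trial steering committee within 24 hours. The section names three possible events: pressure wounds, aspiration and cardiac arrest.

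Section 8.2 plans interim analyses after 120 and 180 patients. It allows termination for safety on either of two grounds: an unexpected rise in intubation in the intervention group, or "increased occurrence of severe or unexpected adverse events". The provision is permissive and carries no numerical safety threshold.

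The ethics section (3.2, Ethical considerations) commits the trial to "standards of Good Clinical Practice (as defined by the International Conference on Harmonisation") but reproduces no definition of a serious event.

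**The concern.** There are two separate defects, both in what the Protocol states.

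The first is the seriousness list. It is worded as closed, and none of its items looks at the lasting consequence of an event or at its effect on length of stay. The intervention is positional, with a target of 16 hours in 24, and pressure wounds are the first possible event that the Protocol names. An injury that leaves permanent harm, or delays discharge, can therefore be correctly classified as non-serious under the Protocol and stay outside the 24-hour route.

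The second is the link between sections. Section 9 sorts events by seriousness, whereas 8.2 acts on severity or unexpectedness. Severity is not defined or graded anywhere in the Protocol, so those conducting the interim analysis are not told which of the reported events count.

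At stake are the speed with which the steering committee learns of some lasting injuries and the clarity of the only safety ground based on adverse events. The primary analysis is not affected.

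**Working it through.** No figure in the plan bears on this point, so the check sets the provisions side by side.

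**Step 1. Test the events that the Protocol names against the four criteria.**

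| Event | Serious under section 9? |
|---|---|
| Cardiac arrest | Yes, criterion 2 |
| Aspiration | Yes, whenever it is life-threatening, needs a higher level of care or needs preventive intervention |
| Pressure wound treated to stop it worsening | Can be, criterion 4 |
| Pressure wound, or other positional injury, that leaves lasting harm or delays discharge and meets none of the four | No |

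The gap is the last row.

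**Step 2. Ask whether criteria 3 and 4 close the gap.** Criterion 4 concerns preventing a worse event; it does not address harm already done. Criterion 3 has little room to operate in a patient already in intensive care, and the Study setting section places part of the intervention there. Neither closes the gap reliably.

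**Step 3. Follow such an event through the reporting routes.** It goes to the principal investigator, because section 9 collects PP-related events whether serious or not. It does not go to the steering committee within 24 hours.

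**Step 4. Compare the terms in section 9 and 8.2.**

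| | Section 9 | Section 8.2 |
|---|---|---|
| Classifying term | Serious, by four criteria | Severe, undefined |
| Expectedness | No step for judging it; a list of possible events | Unexpected events count |

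The three listed events would naturally be read as expected. For them, the adverse-event route into 8.2 then rests on the undefined word. The other safety trigger, a rise in intubation, is not a measure of pressure injury. An unlisted injury could enter 8.2 as unexpected.

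**Step 5. Size.** The documents give no rate for injuries in the last row of step 1. For scale only, assume 2% to 5% of PP-arm patients have one. The planned PP arm is 240 / 2 = 120, giving 120 × 0.02 = 2.4 to 120 × 0.05 = 6.0 patients over the whole trial. At the first interim analysis the arm holds about 120 / 2 = 60, giving 60 × 0.02 = 1.2 to 60 × 0.05 = 3.0. Neither percentage has support in the documents, and the conclusion does not depend on them.

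**The case against.** A reader might infer that the main injuries to be expected from proning escape both expedited reporting and the stopping provision. The documents do not support that:

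- Cardiac arrest is serious under criterion 2. Many aspirations, and pressure wounds treated to prevent worsening, already meet one of the four criteria.
- Section 8.2 is not tied to seriousness. It is discretionary, it also covers unexpected events, and it has a separate intubation ground. A non-serious classification does not bar an event from being considered.
- All PP-related events reach the principal investigator. Complications, and in-hospital and ICU length of stay, are secondary outcomes in section 7.2, so these injuries need not go unseen.
- The fields of the reporting form are not shown. It cannot be said that severity goes unrecorded, only that the Protocol does not define it.

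All of this stands, and it narrows the point.

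It can also be argued that the two missing criteria are a preference, since nothing in the Protocol contradicts a four-item list and the Good Clinical Practice standard is cited without its definition. That is only partly persuasive. The general commitment neither supplies the criteria nor overrides an explicit list, and sites will apply the list. The trial also treats length of stay as an outcome worth measuring, which sits poorly with an event classification that ignores it. The mismatch between 8.2 and section 9 needs no outside benchmark at all.

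**Conclusion.** The point holds in a limited form. The seriousness list omits lasting disability and prolonged hospital stay. A prone-related injury with only those consequences is therefore non-serious and misses the 24-hour report to the steering committee, while still reaching the principal investigator. Severity in 8.2 is undefined and does not correspond to seriousness in section 9, which leaves the safety ground ambiguous for the listed events; it does not shut them out.

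This rests on reading the four criteria as exhaustive, as they are worded, and on the listed events being treated as expected, which the Protocol implies but does not state. The number of events affected cannot be derived from the documents. It is a flaw in a stated rule that is cheap to correct and worth correcting, because it concerns how promptly participant harm is escalated.

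**What to change.** In section 9, add two seriousness criteria: *prolongs hospital stay* and *results in persistent or significant disability or incapacity*.

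In 8.2, change the adverse-event ground to *serious (as defined in section 9) or unexpected adverse events*. Two cautions apply:

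- Keep the unexpected-event ground. Replacing the whole phrase by serious events alone would narrow the provision.
- Do not add a between-arm comparison while section 9 collects only PP-related events. Section 5.1.2 allows PP in the standard care arm at the physician's discretion, but control patients who are not proned could contribute almost no events, so the comparison would not be interpretable.

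The two changes belong together. Aligning 8.2 with an unextended list would carry the gap in section 9 into the safety ground.

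The cost is a short amendment, an update of the reporting form and a somewhat higher count of serious events, with correspondingly more 24-hour reports.

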## 10. PRONE META-TRIAL

Data will be shared for meta-analysis of the effect of prone positioning in Covid-19 patients with the PRONE group, based on six multicenter randomised controlled trials with almost identical design, started in parallel during the first wave of the pandemic. A Data Transfer Agreement shall be signed before transfer of data.

